## Abstract

**Background:**

A majority of adolescents do not meet the recommended levels of physical activity, while reported levels of mental health problems are increasing, and socioeconomic disparities in academic performance are widening. Many schools are implementing physical activity in different forms, but there is inconclusive evidence on what types of interventions improve mental health, cognitive functions, and academic performance and how to implement such interventions. There is a critical need for integrated, feasible, and equitable interventions. The objective of this study is to develop an effective multi-component school-based intervention that will target both physical activity and homework support during an extended school day and evaluate its effects on mental health, cognitive function and academic performance.

**Methods:**

The study is designed as a cluster-randomised controlled trial with 54 schools and approximately 2,700 students in grade 8 (age 14–15). The intervention includes three weekly 60-minute sessions: (1) Different types of physical activities (2), Homework support with short activity breaks, and (3) Walking and listening to audiobooks. This study will evaluate both outcome effects and implementation process. The primary outcome is anxiety, assessed using the Spence Children’s Anxiety Scale (SCAS-S). Secondary outcomes include physical activity, sedentary time and behaviours measured by accelerometry and questionnaire, cognitive functions assessed by a computer-based test battery, mental health and sleep with questionnaires, and academic performance by grades. Process evaluation will include fidelity, dose, feasibility, acceptability and context, using structured documentation, interviews, focus groups, and observations.

The effectiveness of outcomes between groups will be assessed using mixed-effects regression analysis, adjusting for relevant covariates. Process data will be analysed using descriptive statistics and content, and thematic analysis.

**Discussion:**

This study addresses key knowledge gaps in school-based health promotion by integrating physical activity and homework support within the school structure. The results will yield insights into both effectiveness and implementation, informing future policy and practice in schools to promote health and facilitate students’ learning. The intervention targets youth in diverse socioeconomic contexts and is expected to contribute to reducing health and education inequalities.

**Trial registration:**

The trial was retrospectively registered on April 27, 2021. ISRCTN78666212.

**Supplementary Information:**

The online version contains supplementary material available at 10.1186/s12889-026-26469-3.

## Background

Being physically active during adolescence is associated with substantially higher mental and physical health in both the short- and long-term [1]. Despite this evidence, the majority of adolescents both in Sweden and internationally do not meet the physical activity recommendations [2, 3], and activity levels decrease with increasing age [4]. Critically, physical activity levels vary depending on socioeconomic background, where adolescents from families with low education show the lowest levels of physical activity, and lower academic performance [5]. Furthermore, more than half of children from the lowest socioeconomic backgrounds do not complete upper secondary education [6]. In parallel, cardiorespiratory fitness has declined over time [7], while the reported prevalence of mental health problems among Swedish adolescents has increased [8, 9]. Globally, it is estimated that 14% of 10–19-year-olds suffer from mental health conditions [10].

The prevalence of self-reported psychosomatic health problems has doubled between 1985 and 2018 [11] and 10–15% of children and adolescents have received health care for some form of mental illness [8]. In high-income countries in 2019, psychiatric conditions represented the most significant single contributor to the overall burden of disease among those under 20 years [12]. Anxiety is the mental health condition that increases most rapidly. Still, there is an evident lack of studies about anxiety in children and adolescents [9]. Evaluation of interventions and methods to promote mental well-being and prevent mental health problems is needed [9]. Mental health problems in early life are related to a higher risk of developing prolonged and more severe mental illnesses later, as well as poorer academic performance [8, 13, 14]. Adding to this, adolescents report decreased time in reading, and there is now a larger variation between students from different socioeconomic groups in reading comprehension compared to earlier education results [15].

Given such longitudinal trends in mental health, physical activity, fitness, and academic performance, it has been acknowledged that increasing levels of physical activity may represent an impactful intervention in adolescents. Physical activity has indeed been shown to be positively related to mental health, cognition, and academic performance in children and adolescents [16–18]. Adolescents who engage in more physical activity than their peers have reported positive effects on psychosocial outcomes and academic achievement [19]. Similar results have been reported in studies on twins, where a more active monozygotic twin reports higher mental health, compared to the less active twin, both cross-sectionally and longitudinally [20]. This renders an argument that at least some of the results from observational data can be regarded as causal, and gives the rationale for intervention studies in an applied setting. However, the evidence to date on the effects of school-based physical activity interventions on mental health, cognitive function and academic performance has not been consistent [17, 21, 22]. Of critical importance, school interventions have not been effective at actually increasing children’s physical activity, and there is a need for better implementation [23, 24]. More research is therefore needed to determine how school interventions, including physical activity, can be designed and implemented to be effective for increasing physical activity and improving mental health, cognitive function and academic performance in adolescents.

To better understand what type of strategies and implementation are effective for adolescents, more research is needed to understand how and what interventions and environmental factors can make an intervention more or less successful in their intended practice settings [25]. One of the challenges of school-based interventions is that teachers tend to identify time constraints as a major barrier to implementing physical activity programmes [26]. To address such barriers and enhance implementation, one important approach is to involve school staff and students in the planning process [27]. Such a research approach effectively generates knowledge that target groups find trustworthy, facilitating the transfer of evidence into practice [27].

Importantly, a change in the organisational structure by extending the school day represents a promising strategy for school-based programmes aiming to mitigate the impacts of social inequalities on adolescents’ health outcomes. Extending the school day additionally holds promise for improved implementation of homework support programmes, which tend to suffer from high attrition, sporadic attendance and mixed results relating to academic performance and behaviour [28, 29].

## Objective

The objective of this study is to develop an effective multi-component school-based intervention that will target both physical activity and homework support during an extended school day and evaluate its effects on mental health, cognitive function, as well as academic performance.

### Scientific research questions

What are the effects of a school-based programme including physical activity and homework support during an extended school day on mental and physical health, physical activity, cognitive function, and academic performance?Are there any differences in the effects of the intervention in relation to gender, socioeconomic status, and neurodevelopmental conditions (e.g. ADHD, autism)?How is the programme implemented with regard to fidelity, dose, feasibility, acceptability, and context? What are the barriers and facilitators identified in the implementation of the intervention?

## Methods

### Study design

This study will be carried out as a cluster-randomised parallel trial, with schools as the unit of randomisation and a wait-list control group. The list of schools that will participate will be computer-randomised either to intervention or control with a 1:1 ratio. The randomisation will be performed by a statistician in blocks of two and will be done separately for low and high socioeconomic status schools. The personnel recruiting the schools did not have access to the randomisation sequence. The protocol is reported in accordance with the SPIRIT (Standard Protocol Items: Recommendations for Interventional Trials) 2025 guidelines [30].

### Recruitment of schools, participants and setting

Schools from the Stockholm area within a 2–3 h drive from the Swedish School of Sport and Health Sciences and schools in the counties of Småland, located in the south of Sweden, will be invited by e-mail to the headteachers and vice headteachers. Schools with a sports profile and schools with a student population not speaking Swedish will be excluded.

Fifty-four schools with 2700 adolescents in grade eight, aged 14–15 years, will be included by the research group. Three waves are planned: the first in the school year of 2021–2022, the second in 2023–2024, and the third in 2024–2025. A one-year follow-up will be performed in the spring of 2025 and 2026.

### The intervention

A logic model of the intervention study, including the intervention components, process evaluation, and outcome evaluation, is described in Table 1.

**Table 1 Tab1:** Logic model of the intervention study

Input	Intervention components	Materials	Implementation strategies	Mediators	Process outcomes	Outcome evaluation
Funding Expert support	Physical activities Homework support with short activity breaks Walking and audiobook	Physical activity inspirational material Digital audio book subscriptions	Workshops with school staff Parental meetings Research support	Competence Autonomy Relatedness	Fidelity Dose Feasibility Acceptability Context	Mental health Cognitive function Academic performance Physical activity Sedentary behaviour Health behaviours BMI

The development of the intervention has been directly informed by barriers and facilitators identified by students and teachers [31]. This information was collected through workshops and interviews during 2021–2022 and used to develop implementation strategies for this study.

### Intervention components

This multi-component intervention will be performed during an extended school day, 60 min three times per week, for six months and include three components described below. The intervention activities will be included as part of the mandatory school curriculum for all the students in the intervention schools.Different types of physical activities (1 × 60 min per week). The physical activities will be chosen in collaboration with teachers and students, and will take place in both indoor school facilities and outdoor areas. Examples of activities are swimming, dancing, gym, circuit training and ball sports, to suit all interests.Homework support with short activity breaks, 3–5 min every 30 min (1 × 60 min per week).Walking and listening to an audiobook (1 × 60 min per week), in areas nearby the school.

To make the programme integrated and sustainable, the activities can be scheduled at any time during the school day and will be led by school staff.

### Theoretical framework

The intervention is based on evidence-based principles for supporting sustainable motivation and behaviour [32, 33]. The intervention is based on the Self-Determination Theory (SDT), which focuses on human motivation, particularly the three basic psychological needs of competence, autonomy, and relatedness. The intervention includes different types of physical activities, homework support with short activity breaks, and walking while listening to an audiobook. Participating in physical activities is expected to enhance physical skills and competence. The students will be able to choose physical activities that will promote their autonomy. The social and collaborative dimension of the activities also strengthens social bonds and the sense of relatedness. With a short activity break, homework support is expected to support the student’s sense of autonomy and competence. It will also create a supportive learning environment that enhances relatedness.

To optimise adherence, school staff will participate in workshops to improve their knowledge about health and learning and to plan and develop delivery plans for the intervention at the beginning of each wave. These workshops aim to enhance both staffs’ and students’ autonomy, competence, and relatedness. By aligning the intervention components with the principles of SDT, the programme creates a motivating and supportive environment for students, ultimately enhancing their overall well-being and academic performance.

### Implementation strategies

Several implementation strategies will be conducted to optimise adherence. These strategies include workshops, parental meetings, support from researchers, and inspirational material.

### Workshops with school staff

The school staff in the intervention schools will participate in workshops with the research team to plan how to design and implement the intervention in their schools. The workshops will focus on (1) feasible implementation strategies for the intervention components in each school and (2) how to enhance students’ and teachers’ involvement. An initial intervention delivery plan will be established at the end of the workshop. The school headteacher will be asked to provide facilities and extra time/hours for school staff to perform the intervention.

### Parental meetings

Parental meetings to inform about the study will be conducted in all intervention schools at the beginning of each school year. In these meetings, the researchers will give a short lecture about physical activity and health among adolescents and provide information about the study. The parents will have the opportunity to ask questions during the meeting.

Since the activities will be scheduled and mandatory for all students in intervention schools, the schools will also inform the parents of these activities at the beginning of the school term through their regular channels.

### Research support

Researchers will continuously visit all intervention schools to support the teachers with strategies on how to deliver the activities.

### Materials

All intervention schools will receive (1) Physical activity inspirational material, including digital material for the activity sessions, and activity cards for the activity breaks during the homework sessions, and (2) Digital audiobook subscriptions to use during the walking sessions.

### Control group

The control group will have unchanged school schedules and will be offered the intervention after the post-intervention measurements in the following school year.

### Outcome evaluation

This intervention study will evaluate both outcomes and the implementation process with quantitative and qualitative methods.

#### Data collection

Data for the outcome measures will be collected before and after the intervention. Baseline data will be collected in the autumn of 2021 (first wave), autumn 2023 (second wave), and autumn 2024 (third wave). Post-intervention data will be collected in the spring of 2022 (first wave), spring of 2024 (second wave), and spring of 2025 (third wave). One-year follow-up measures will be collected in the spring of 2025 and 2026. Data for the process evaluation will be collected continuously during the intervention (observations and documentation) during the school years: 2021–2022, 2023–2024, and 2024–2025. All measurement methods and routines have been tested with adolescents in the school setting.

Students in both the intervention and control groups will receive a gift card worth 150 SEK (≈ 15 €) as compensation after each measurement. Additionally, participants in the intervention group will receive audiobook subscriptions during the intervention while those in the control group will receive the same after the follow-up measurements.

#### Measurements

The measurements will be conducted by trained healthcare professionals and researchers who visit the schools and carry out the assessments before lunch on the test days. These measurements include questionnaires administered via a secure online survey tool, accelerometers to assess physical activity and sedentary time, height and weight measurements, and a cognitive test battery.

The parents, teachers or teachers’ assistants of physical activity sessions and headteachers also fill out online questionnaires. Reminders will be sent by e-mail and text messages up to three times.

##### Primary outcome

Anxiety will be assessed with the Spence Children’s Anxiety Scale Short Version (SCAS-S) questionnaire, including 19 items, which has been shown to be valid and reliable for this age group [34]. Anxiety will also be assessed with a subscale of the Measurement of Mental Health Among Adolescents and Young People at the Population Level (MMAPP) scale. The MMAPP comprises two subscales, depression and anxiety [35]. The instrument has been translated and culturally adapted for use in Sweden through a multi-step process involving direct engagement with adolescents and is currently undergoing validation [35].

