### Sample size calculation

To obtain an effect size of intervention Cohen’s d = 0.35 in anxiety (based on a meta-analysis [18]) in a population with the average correlation between cluster of 0.02, a variance of 5 points in the primary outcome SCAS-S, a two-tailed significance test (α = 0.05), and a power of 80%, it is required to include at least 27 schools in the intervention group and 27 schools in the control group with 50 students from each school. Anxiety will be assessed with the questionnaire Spence Children’s Anxiety Scale Short Version (SCAS-S) [34].

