### Data analysis

Baseline differences in continuous demographic variables between the intervention and control groups will be presented using means and standard deviations (SD) for normally distributed data and compared using independent t-tests. For non-normally distributed data, medians and ranges will be reported, with analyses conducted using non-parametric tests. Categorical variables will be described as proportions, and group differences will be examined using chi-square tests. The effects of the intervention on primary and secondary outcomes will be analysed through mixed-effects regression models with two hierarchical levels (individual and school), using post-intervention data and following the intention-to-treat approach. Initially, a crude model will be tested for each outcome at post-intervention, including group allocation as a predictor and adjusting for baseline values of the corresponding outcome. In a second model, gender and parental education will be added to the model. Interactions between group and gender, or group and parental education, will be tested and, if significant, analysed using stratified models All participants with baseline measurements will be included, and missing data will be addressed using multiple imputation The potential impact of missing data on the results will be evaluated through sensitivity analyses. Additionally, the analysis will be performed per protocol, including only those participants with high fidelity to the intervention components. All analyses will be performed blinded to group allocation. The data analysis plan was submitted as part of the trial registration (ISRCTN78666212).

All focus groups and interviews will be audio-recorded, transcribed verbatim, and analysed using qualitative analysis, including content [50–52]- and thematic analysis [53, 54]. The documented data on dose and fidelity will be analysed with descriptive statistics.

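### The Primary outcome section leaves the MMAPP anxiety subscale unranked beside SCAS-S, and Data analysis gives two models without saying which one decides or including the randomisation stratum

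*Protocol article*

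**What the plan says.** **Instrument.** The abstract ties the primary outcome to one scale: "The primary outcome is anxiety, assessed using the Spence" Children's Anxiety Scale. The sample size section does the same, with "a variance of 5 points in the primary outcome SCAS-S", and sizes the trial on that scale alone at a two-sided 5% level. The Primary outcome section opens with SCAS-S, a "questionnaire, including 19 items, which has been shown to be valid and reliable for this age group". It then continues: "Anxiety will also be assessed with a subscale of the Measurement of Mental Health Among Adolescents and Young People at the Population Level (MMAPP) scale". It says of MMAPP that it "is currently undergoing validation". The Secondary outcomes section lists the other mental health scales but not MMAPP, so the subscale appears only under the primary heading.

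**Model.** Data analysis fixes the time point (post-intervention), the intention-to-treat approach and a two-level mixed model with students within schools. It then says: "Initially, a crude model will be tested for each outcome at post-intervention", with group and the baseline value of that outcome as predictors. A second model adds gender and parental education. The article does not say which model carries the primary claim.

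**Stratum.** Study design says schools are randomised in blocks of two, separately for low and high socioeconomic status schools. That school-level factor is in neither model.

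Data analysis also says that an analysis plan was lodged with the trial registration. That plan is not shown.

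**The concern.** A confirmatory claim needs one endpoint, one time point and one test. The time point is fixed here. The section that defines the endpoint disagrees with the two other places that name it, and the test is given in two forms.

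If the deciding result can be chosen after both are seen, the error rate of the primary claim exceeds the 5% used for sizing. A reader who relied on the Primary outcome section alone could also let the claim rest on the instrument whose validation the article describes as unfinished. The article records that registration was retrospective, so clear wording in the published protocol is worth more than usual.

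**Working it through.** **1. Which instrument is primary?**

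| Place | Primary instrument |
|---|---|
| Abstract, Methods | SCAS-S only |
| Sample size calculation | SCAS-S only |
| Primary outcome | SCAS-S, then MMAPP anxiety, unranked |
| Secondary outcomes | MMAPP not listed |

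Two explicit statements favour SCAS-S and none names MMAPP as primary. The Primary outcome section is therefore the text out of line.

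**2. The plan's own error rate.** The only level stated is two-sided 0.05, for SCAS-S. One instrument tested in one model gives 5.0%. This is the figure to compare against. (Whether 27 schools per arm follows from the sizing inputs is a separate matter and is not used here.)

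**3. SCAS-S fixed, model open.** For two test statistics Z1 and Z2 that are bivariate normal with correlation ρ under the null hypothesis, the chance that at least one is significant is

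1 − P(|Z1| < 1.96 and |Z2| < 1.96).

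The two models share outcome, students, baseline covariate and school level, and differ only by gender and parental education, so ρ should be high. The documents give no value. The values below are assumptions.

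| Assumed ρ between models | Either-model error |
|---|---|
| 0.99 | 5.7% |
| 0.95 | 6.5% |
| 0.90 | 7.0% |

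**4. Model fixed, instrument open.** The same formula applies, but only if MMAPP anxiety were co-primary and significance on either scale were enough.

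| Assumed ρ between instruments | Either-instrument error |
|---|---|
| 0.9 | 7.0% |
| 0.8 | 7.8% |
| 0.6 | 8.8% |
| 0.5 | 9.1% |
| 0 (upper bound) | 1 − 0.95² = 9.75% |

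**5. Stratum.** Allocation is balanced within low and high socioeconomic status schools. Parental education is a student-level variable and captures only part of a school-level factor. Leaving out a stratification factor that predicts the outcome usually makes the test somewhat conservative and costs precision, so it does not add to the inflation in step 3. The documents give no figure from which to size the loss.

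**The case against.** The strongest reply is that the instrument is not open at all. SCAS-S is named as primary twice, the trial is sized on it, it comes first in the Primary outcome section, and it alone is called validated. MMAPP enters as an additional measure of the same construct. This stands, and it reduces the instrument part to an inconsistency in one section.

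A reader might go further and infer that the primary claim can be won in four ways, two instruments by two models, each at an uncorrected 5%. The documents do not support that. No sentence makes MMAPP co-primary, and none says that significance on either scale or in either model is enough.

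The second reply is that a crude model followed by an adjusted one is ordinary reporting, and that the deciding model is commonly named in the analysis plan, which here is registered but not shown. That plan may settle the question, so the model part is conditional on it. The reply does not remove the conflict inside the article about the endpoint. Nor does it explain why neither stated model carries the factor by which schools were stratified. The abstract's mention of adjustment for covariates does not settle the model either: it names none, and the crude model already adjusts for baseline.

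The third reply is that the two models will nearly always agree. That is largely right, and it is why the inflation in step 3 is small.

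**Conclusion.** The point holds in a limited form. The Primary outcome section contradicts the abstract and the sample size section by leaving MMAPP anxiety unranked beside SCAS-S. SCAS-S is evidently the intended primary outcome, so this is a fault of placement and wording.

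The choice left more open in the article is the model, worth about 5.7% to 7.0% against a nominal 5%. This rests on assumed correlations of 0.99 to 0.90 and on either model being allowed to decide. The 7% to 9% range across instruments (assumed correlations 0.9 to 0.5) applies only if MMAPP were treated as co-primary, which the article does not say.

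The omitted stratum is a mismatch between design and analysis that should be corrected at the same time. The inflation is modest, but the correction is cheap and concerns the primary claim, so it should be made.

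**What to change.** 1. In Primary outcome, state that SCAS-S at post-intervention is the sole primary outcome, and move the MMAPP anxiety subscale to Secondary outcomes.
2. In Data analysis, name one confirmatory mixed model for SCAS-S: group, baseline SCAS-S, gender, parental education and the socioeconomic stratum used in randomisation, with school as random effect. Wave may be added. Call the other model supportive.
3. If the registered analysis plan already names a deciding model, bring the article into line with it and say so.

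The cost is a few sentences, a small change to the stated model and possibly an update to the registered plan. No extra data collection is needed: every covariate is either already planned or known from randomisation.
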